**Appendix**

***Adverse Event Definition:***

*An adverse event (AE) is any untoward medical occurrence in a patient administered a pharmaceutical product and that does not necessarily have a causal relationship with this treatment. An adverse event can therefore be any unfavorable and unintended sign (including an abnormal laboratory finding), symptom, or disease temporally associated with the use of a medicinal product, whether or not related to the medicinal product.* *Pre-existing conditions that worsen after drug administration will be reported as adverse events. Generally an increase/ worsening of pre-existing disease status to more than 30% of baseline are reported as an adverse event. (For eg, a baseline heart rate increase from 150/ minute to more than 195/ minute, an increase of FiO2 requirement from a baseline 50% to more than 65%). This will be predefined and recorded for all infants before the start of cell therapy.*

***Adverse Event Severity and Relationship to hAEC:***

*The severity of AEs will be graded using the National Cancer Institute Common Terminology Criteria for Adverse Events (NCI-CTCAE), v4.0. For AEs that are not identified in the NCI-CTCAE, the following scale will be used:*

*Grade 1 Mild*

*Grade 2 Moderate*

*Grade 3 Severe*

*Grade 4 Life-threatening or disabling*

*Grade 5 Death related to an AE*

*The assessment of causality will be made by the treating physician using the following definitions:*

***Unrelated:***

*This category is applicable to adverse events that are judged to be clearly and incontrovertibly due to extraneous causes (disease, environment, etc.) and do not meet the criteria for drug relationship listed under Unlikely, Possible or Probable.*

***Unlikely:***

*In general, this category is applicable to an adverse event that meets the following criteria (must have the first two):*

*1. It does not follow a reasonable temporal sequence from administration of the drug.*

*2. It may readily have been produced by the patient’s clinical state, environment or toxic factors, or other modes of therapy administered to the patient.*

*3. It does not follow a known pattern of response to the suspected drug.*

*4. It does not reappear or worsen when the drug is re-administered.*

***Possible:***

*This category applies to adverse events for which the connection with hAEC appears unlikely but cannot be ruled out with certainty. An adverse event may be considered possibly related if or when (must have the first two):*

*1. It follows a reasonable temporal sequence from administration of the drug.*

*2. It may have been produced by the patient’s clinical state, environment or toxic factors, or other modes of therapy administered to the patient.*

*3. It follows a known pattern of response to the suspected drug.*

***Probable:***

*This category applies to adverse events that are considered with a high degree of certainty to be related to hAEC. An adverse event may be considered probable, if (must have the first three):*

*1. It follows a reasonable temporal sequence from administration of the drug.*

*2. It cannot be reasonably explained by the known characteristics of the patient’s clinical state, environment or toxic factors, or other modes of therapy administered to the patient.*

*3. It disappears or decreases on cessation or reduction in dose.*

*4. It follows a known pattern of response to the drug.*

*5. It reappears on re-challenge.*

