     1. HLA matching: Allogeneic UCBCs will be obtained from BMDI Cord Blood Bank with an HLA matching of at least 4/6. As HLA matching and processing UCBCs may be time-consuming, the eligibility (neuroimaging) will be reconfirmed before administering the allogeneic UCBCs after successful HLA matching.
     2. Age of administration: Allogeneic UCBCs will be administered via IV infusion anytime from birth until three months of life, generally within 2-3 weeks of diagnosis of confirmed severe preterm brain injury.
     3. Cell infusion: Only one allogeneic UCBC infusion will be administered intravenously.
     4. UCBC dose: The infusion is aimed for 50 million total nucleated cells (TNCs) per kilogram of body weight will be administered. This therapeutic dose is based on preclinical^30^ and clinical studies^5,6^ of UCBC for different types of perinatal brain injury.
     5. Route: The UCBCs will be administered intravenously via a peripheral intravenous cannula.
  2. ***Comparison***

There will be no control group as this is a single-arm, open-label, phase-I study.

- 1. ***Outcomes***
     1. Primary outcomes
        1. Feasibility: Allogeneic UCBC therapy will be considered feasible if there is an availability of at least 4/6 HLA-matched allogeneic UCBCs sourced from the BMDI Cord Blood Bank for >60% of eligible infants.
        2. Safety: Allogeneic UCBCs will be considered as safe if there are no serious adverse events related to UCBCs during and for 48 hrs post-infusion and the absence of GVHD in the first three months after cell infusion. The safety outcomes will be reported for eligible infants where feasibility is demonstrated, and allogeneic UCBCs are administered.
     2. Secondary outcomes
        1. Clinical outcomes: The following clinical outcomes will be reported for the infants who received infusion.
           1. Death, until 24 months of corrected age
           2. Moderate to severe bronchopulmonary dysplasia, assessed as oxygen or positive pressure requirement at 36 weeks of postmenstrual age
           3. Severe retinopathy of prematurity, assessed as any retinopathy requiring anti-VEGF or laser treatment before discharge
           4. Necrotising enterocolitis, assessed as bell stage 2 or more before discharge
           5. Culture-proven sepsis, bacterial or fungal, requiring antibiotics treatment for 7 or more days before discharge

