The criteria for eligibility will be confirmed on the day of infusion. The cell product will be obtained from the BMDI Cord Blood Bank a day before the transfusion. CBU released from the Cord Blood Bank for this study will have undergone all pre-release testing as routinely performed for release for bone marrow transplant, and have met compliance with the AusCord Quality & Release Criteria. The CBU will be released under “Exceptional Release” and the TGA notified as the bank is not licensed for the release of unrelated allogeneic non-homologous use. The product will be thawed at Monash Health Translation Precinct's Cell Therapy and Regenerative Medicine Platform. After thawing, washing of cells (to remove DMSO, a cryopreservant) will be undertaken using Dextran-Albumin and resuspended in 4% albumin as per standard clinical practice. Cell viability (>70% viable CD34+ cells, in accordance with the AusCord Quality & Release Criteria.) will be determined before administration. UCBCs will be administered intravenously (through a peripheral intravenous catheter) within one hour of thaw at a dose of 50 million (as available in aliquot) viable TNCs/ kg body weight. The exact dose will depend on the number of viable TNCs available in the final cell product. The volume of cell infusion(s) will be 10 mL/kg, and cell infusion will occur over one hour undertaken in the neonatal unit or the clinical trials facility of Monash Children's Hospital. The custody of care of the product will be transferred from BMDI Cord Blood Bank to the shipper to Monash Health Translation Precinct's Cell Therapy and Regenerative Medicine Platform to the clinical team using appropriate standard operating procedures.

- 1. ***Statistical analysis***

Descriptive statistics will be used to report demographics and outcomes. The categorical variables will be described as frequency and percentage and continuous variables as median (interquartile range) and mean (standard deviation), depending on the normality of the data, which will be determined by the Shapiro-Wilk test. The data will be analysed using STATA Version 17.0 (StataCorp LLC, College Station, TX, USA). Paired t-tests or Wilcoxon signed-rank tests will be performed to compare the laboratory parameters before and after infusion.

- 1. **Safety monitoring and reporting**
     1. Monitoring **(Figure 1 and Table 1):**
        1. The following will be monitored during and within 48 hours of infusion.
     - During infusion

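### A fatal or persistent SAE with plausible timing and no other explanation fits none of the Appendix causality categories, although the SAE half of primary safety depends on relatedness

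*Combined protocol and SAP*

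**What the plan says.** The primary safety rule (Methods, Outcomes, Primary outcomes) has two halves. The first is "Allogeneic UCBCs will be considered as safe if there are no serious adverse events related to UCBCs during and for 48 hrs post-infusion". The second is "the absence of GVHD in the first three months after cell infusion", to which no relatedness condition is attached.

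The exposure is a single one. Intervention details states "Only one allogeneic UCBC infusion will be administered intravenously", and UCBCs administration adds that "cell infusion will occur over one hour".

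Relatedness is assigned by the treating physician under the Appendix section titled "Adverse Event Severity and Relationship to hAEC". There are four categories: Unrelated, Unlikely, Possible and Probable. There is no Definite category. Probable requires its first three items, and the third is "It disappears or decreases on cessation or reduction in dose". Possible is introduced with "This category applies to adverse events for which the connection with hAEC appears unlikely but cannot be ruled out with certainty" and requires its first two items.

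The Reporting section refers to the NHMRC 2016 guidance. The protocol body then defines adverse event, adverse reaction, serious event or reaction, and suspected unexpected serious adverse reaction. It gives no criteria for judging causality. Nowhere do the documents say which Appendix categories count as related for the primary outcome.

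**The concern.** The third Probable item is a dechallenge test. It suits a product that is given repeatedly or continuously and can be withdrawn. Here the exposure is over after one hour, while the SAE window runs for a further 48 hours. After that hour there is nothing left to stop or reduce, and a death or lasting deterioration cannot abate in any case.

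The SAE criterion allows zero events, so the label on a single event can decide the verdict. If the most clearly attributable serious event has no category, the verdict on it depends on how someone chooses to resolve the gap after seeing the case. The missing definition of related adds to this, because one Possible SAE can turn the verdict either way.

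**Working it through.** The plan states no event rate and no sample-size calculation, so there is no figure to reproduce. The main check is logical.

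**Inputs.** These are the mandatory items of each category in the Appendix. Let T mean the event follows the infusion in reasonable time, A mean another explanation is reasonable, and D mean the event abates on stopping or reducing the product.

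- Unrelated: clearly due to outside causes, and none of the other categories met.
- Unlikely: not T, and A.
- Possible: T and A.
- Probable: T, not A, and D.

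**Result.**

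| T | A | D | Category as written | Category if D is not mandatory |
| --- | --- | --- | --- | --- |
| yes | yes | yes | Possible | Possible |
| yes | yes | no | Possible | Possible |
| yes | no | yes | Probable | Probable |
| yes | no | no | none | Probable |
| no | yes | either | Unlikely | Unlikely |
| no | no | either | none, unless clearly extraneous | unchanged |

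The fourth row is the defect. Take a death some hours after the infusion that nothing else explains. It is not Unrelated, because no outside cause is clear. It is not Unlikely, because the timing is plausible. It is not Possible, because that needs an alternative cause. It is not Probable, because it cannot abate. Removing D from the mandatory items moves this row to Probable and changes no other row. The last row is also open, but an event without plausible timing is not the harm signal at issue.

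**Illustration of size, on assumed rates.** Let p be the true proportion of infants with a related SAE in the window, and u the share of those events that fall in the gap and are not counted as related. All other related events are taken as counted. Then

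P(no counted event among n infants) = (1 − p(1 − u))^n.

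For p = 10% and n = 20: with u = 0, 0.90^20 = 0.122; with u = 25%, 0.925^20 = 0.210; with u = 50%, 0.95^20 = 0.358.

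| n | p | u = 0 | u = 25% | u = 50% |
| --- | --- | --- | --- | --- |
| 20 | 5% | 0.358 | 0.466 | 0.603 |
| 20 | 10% | 0.122 | 0.210 | 0.358 |
| 20 | 20% | 0.012 | 0.039 | 0.122 |
| 10 | 5% | 0.599 | 0.682 | 0.776 |
| 10 | 10% | 0.349 | 0.459 | 0.599 |
| 10 | 20% | 0.107 | 0.197 | 0.349 |

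The values of n are the planned total and one stratum. The Sample size section warns that fewer may be infused.

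**The case against.** The strongest reply is that the gap is narrow and that oversight does not depend on it.

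- A reader might infer that any SAE caused by the infusion escapes the scale. The documents do not support that. An event that starts during the infusion and abates when it is stopped can meet the third Probable item, and infusion reactions are among the risks that the protocol names.
- Possible asks only that the clinical state may have produced the event. These infants have severe brain injury, and the protocol's local data put mortality with severe IVH at 43%. Most serious events will have a plausible alternative cause and will be Possible.
- A reader might infer that such an event could be hidden. It could not. All SAEs go to the DSMB and HREC within 7 days, whether related or not, and both bodies review the trial's safety after a serious event.
- A reader might take hAEC to mean that the scale governs a different product. The term is a leftover label in the section heading and in Possible and Probable. Elsewhere the scale speaks of the drug, and no hAEC is given in this trial. The slip is editorial.
- The physician could simply choose the nearest category, and the NHMRC reference might supply another scale.

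The first four points stand and limit the scope. The last does not close the gap. The Appendix directs the physician to its own definitions, and choosing the nearest category means setting a mandatory item aside. Possible would also be a poor fit, since it describes a connection that appears unlikely. The content of the NHMRC guidance is not in the documents, and the protocol takes no causality criteria from it.

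**Conclusion.** The point holds in a limited form and should be fixed. Read literally, the scale has no category for an SAE that is plausibly timed, has no other reasonable explanation, and is fatal or persistent. This is a fault in a stated rule, and it affects the label used in the SAE half of the primary safety verdict. It does not affect the GVHD half, the reporting of the event, or DSMB and HREC oversight.

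The logical result needs no assumption beyond reading the mandatory items as mandatory. How often it would matter cannot be derived from the documents. The probabilities above rest wholly on assumed p and u, and on unclassified events being left out of the count. They show direction and possible size, and are not a forecast. A reader might go further and infer that a favourable verdict is built in. That does not follow, because Probable can still be met by events that abate on stopping, and Possible SAEs may count as related once the term is defined.

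**What to change.** 1. In the Appendix, make only the first two Probable items mandatory (plausible timing, no other reasonable explanation). Keep dechallenge and re-challenge as supportive items where they can be assessed.
2. Replace hAEC with allogeneic UCBCs in the causality heading and in Possible and Probable. This is editorial.
3. Before analysis, state under Primary outcomes which categories count as related. Report the safety result both with and without Possible events, so that a verdict resting on one such event is visible.

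The cost is a wording amendment with HREC approval, as the Ethics section requires for any amendment. Visits, sample size and data collection do not change. The downside is that some events that now have no category will count as related, so the safety criterion becomes slightly harder to meet. If Possible is included in the definition of related, the effect could be larger, because alternative explanations will be common in these infants and the rule tolerates no event. That is the reason for reporting both versions. Who makes the final classification is a separate choice, and this correction does not depend on moving it from the treating physician to the DSMB.

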***Serious Adverse Event Definition:***

*A serious adverse event (SAE) is any untoward medical occurrence that occurs at any dose. An AE in a clinical trial is designated to be serious if it results in death, is life-threatening, requires inpatient hospitalisation, or prolongs existing hospitalisation, results in persistent or significant disability or incapacity.*
